## Abstract

**Background:**

Severe hypoglycaemia still represents a significant problem in insulin-treated diabetes. Most patients do not experience severe hypoglycaemia often. However, 20% of patients with type 1 diabetes experience recurrent severe hypoglycaemia corresponding to at least two episodes per year. The effect of insulin analogues on glycaemic control has been documented in large trials, while their effect on the frequency of severe hypoglycaemia is less clear, especially in patients with recurrent severe hypoglycaemia. The HypoAna Trial is designed to investigate whether short-acting and long-acting insulin analogues in comparison with human insulin are superior in reducing the occurrence of severe hypoglycaemic episodes in patients with recurrent hypoglycaemia. This paper reports the study design of the HypoAna Trial.

**Methods/design:**

The study is a Danish two-year investigator-initiated, prospective, randomised, open, blinded endpoint (PROBE), multicentre, cross-over trial investigating the effect of insulin analogues versus human insulin on the frequency of severe hypoglycaemia in subjects with type 1 diabetes. Patients are randomised to treatment with basal-bolus therapy with insulin detemir / insulin aspart or human NPH insulin / human regular insulin in random order. The major inclusion criterion is history of two or more episodes of severe hypoglycaemia in the preceding year.

**Discussion:**

In contrast to almost all other studies in this field the HypoAna Trial includes only patients with major problems with hypoglycaemia. The HypoAna Trial will elucidate whether basal-bolus regimen with short-acting and long-acting insulin analogues in comparison with human insulin are superior in reducing occurrence of severe hypoglycaemic episodes in hypoglycaemia prone patients with type 1 diabetes. http://www.clinicaltrials.gov: NCT00346996.

## Background

Severe hypoglycaemia still represents a significant risk for many patients with type 1 diabetes. The condition is feared by patients [1,2] and relatives [3] and remains a major barrier in achieving recommended glycaemic targets [4]. Moreover, severe hypoglycaemia may, although rarely, lead to permanent brain damage or death [5]. The frequency of severe hypoglycaemia in type 1 diabetic populations is 1–1.7 episodes per patient-year [6-14]. The distribution of episodes is, however, very skewed. Thus, 20% of patients with type 1 diabetes experience two or more episodes of severe hypoglycaemia per year [15]. Once prone to recurrent severe hypoglycaemia, patients often remain so throughout their life.

Insulin analogues were developed to improve treatment of insulin-treated diabetes with respect to glycaemic control and avoidance of hypoglycaemic episodes. Short-acting insulin analogues (aspart, lispro and glulisine) were designed to mimic the fast physiological postprandial insulin release and long-acting insulin analogues (detemir and glargine) were designed to mimic the basal continuous insulin release with minimal peak action, thereby leading to a presumed decreased risk of hypoglycaemia. The effect of insulin analogues on glycaemic control has been documented in large trials [16,17]. However, for several reasons the impact of insulin analogues on the frequency of severe hypoglycaemia is less clear. Firstly, most studies comparing the effects of human insulin with those of insulin analogues specifically exclude patients at risk of severe hypoglycaemia, such as patients with previous severe events or impaired hypoglycaemia awareness, from participation [18-21]. This renders the trials insufficiently statistically powered to detect differences in the frequency of severe hypoglycaemia and the conclusions from these studies can not readily be extrapolated to patient groups prone to severe hypoglycaemia. Secondly, hypoglycaemia is often less well defined and detected, at best as a secondary endpoint, with reports including a mixture of mild, severe, and asymptomatic hypoglycaemia. Thirdly, severe hypoglycaemia should be analysed according to a statistic model that takes into account the much skewed distribution of episodes e.g. negative binomial or zero-inflated models [22].

A Cochrane review comparing short-acting insulin analogues with human insulin included 49 studies, of which 10 studies were eligible in relation to hypoglycaemia [16]. The analysis showed that the overall mean occurrence of hypoglycaemic episodes was lower for short-acting analogues in comparison to regular insulin in patients with type 1 diabetes (−0.2 per patient per month (95% confidence interval: -1.1 to 0.7)). No statistical comparative calculations were possible specifically addressing severe hypoglycaemia due to inconsistent and bias-prone definitions in the different studies. However, in the analogue group the incidence of severe hypoglycaemia ranged from 0–247 (median 22) episodes per 100 patient-year compared to the incidence in the human insulin group ranging from 0–544 (median 46).

After the initiation of the present study, a meta-analysis based on 20 studies (duration > 12 weeks) was published comparing long-acting insulin analogues with long-acting human insulin in type 1 diabetes, including 12, 15 and 13 studies analysing any hypoglycaemia, severe hypoglycaemia, and nocturnal hypoglycaemia, respectively [17]. The analysis showed that long-acting analogues are not associated with a significant reduction of overall risk of any hypoglycaemia in comparison with NPH insulin. When episodes of severe hypoglycaemia and nocturnal hypoglycaemia were separately analysed, insulin detemir, but not insulin glargine, was associated with a reduced risk compared to human NPH insulin (OR 0.73 (0.60 - 0.89), p = 0.002 and OR 0.69 (0.55 - 0.86), p = 0.001; respectively). There are important limitations with the meta-analysis. Firstly, the trials use different criteria for hypoglycaemia, different methods in recording severe hypoglycaemia, and many trials are not randomised. Secondly, the participants in the studies are relatively young (mean: 34 years) with a short duration of diabetes (mean: 13 years) suggesting that the participants’ state of hypoglycaemia awareness is relatively unaffected. Thirdly, in some trials the number of insulin injections per day are different in the human insulin group and the insulin analogue group. Finally, the vast majority of the trials in the analysis were sponsored by manufacturers of long-acting insulin analogues. To our knowledge a direct comparison of long acting insulin analogues and long-acting human insulin has not been made in patients at high risk of severe hypoglycaemia.

When it comes to patients at high risk of severe hypoglycaemia, who may have the greatest potential benefit from insulin analogue therapy, there is only one small, randomised,12-month cross-over study comparing the effect of the short-acting insulin analogue (lispro) and regular human insulin on the frequency of severe hypoglycaemia [23]. The study population comprised 33 patients with type 1 diabetes and hypoglycaemia unawareness. There was a trend towards a lower incidence of severe hypoglycaemia during treatment with insulin lispro in comparison with human insulin (p = 0.087). Another study in 322 women with type 1 diabetes, who were pregnant or planning pregnancy and therefore being at relatively high risk of severe hypoglycaemia due to very tight glycaemic control, compared insulin aspart with human insulin as meal-time insulin (with human NPH insulin as basal insulin) using an open-label, randomised, parallel-group, multicentre design. Although the risk of severe hypoglycaemia in women treated with insulin aspart was 28% lower, the difference did not reach statistical significance [24]. In a randomised 24-week pilot study of 15 patients with type 1 diabetes complicated by severe hypoglycaemia, comparing rigorous hypoglycaemia avoidance with insulin analogue therapy (lispro and glargine), continuous subcutaneous insulin therapy (CSII) or education alone (but not including any control group), hypoglycaemia awareness was restored and further severe hypoglycaemia was prevented with concomitant improvement in glycaemic control in the analogue and CSII groups [25].

The HypoAna Trial is designed to elucidate whether short-acting and long-acting insulin analogues (insulin aspart and insulin detemir) in comparison with human regular and NPH insulin are superior with respect to reducing the occurrence of severe hypoglycaemic episodes in patients with recurrent hypoglycaemia. There is an urgent need for this evidence in clinical practice and a need to elucidate if the higher costs of insulin analogues are justified in this respect. However, since the structures of different insulin analogues are not similar, the results of this study cannot be directly extrapolated to other insulin analogues (lispro, glulisine and glargine).

## Objective

The primary objective is to evaluate the effect of treatment with insulin analogue and human insulin over the preceding 9 months in each treatment arm on the incidence of severe hypoglycaemia in patients with type 1 diabetes prone to hypoglycaemia.

The secondary objectives are – with reference to the ADA criteria for classification of hypoglycaemia [26] – to evaluate the effects of insulin analogue and human insulin from 3 to 12 months of treatment on the incidence of:

· documented (mild) symptomatic hypoglycaemia.

· asymptomatic hypoglycaemia.

· severe hypoglycaemia, documented symptomatic hypoglycaemia, and asymptomatic hypoglycaemia during daytime.

· severe hypoglycaemia, documented symptomatic hypoglycaemia, and asymptomatic hypoglycaemia during night-time

## Methods/design

### Design

The study is a Danish two-year, investigator-initiated, prospective, randomised, open, blinded endpoint (PROBE), multicentre, cross-over trial investigating the effect of insulin analogues versus human insulin on the frequency of severe hypoglycaemia (Figure 1). Patients are randomised to treatment with basal-bolus therapy with insulin detemir and insulin aspart (Levemir®/Novorapid®) or human NPH insulin and human regular insulin (Insulatard®/Actrapid®), in random order. Doses of insulin are adjusted according to individual patient need at the discretion of the investigator. Thus, a treat-to-target design is deliberately not used in order not to intervene with present glycaemic control and everyday clinical practice, which otherwise in itself will interfere with the risk of hypoglycaemia. The best obtainable glycaemic control for the individual patient is strived for in both treatment periods. The protocol did not specify the timing and number of insulin injections per day. In general, a four times daily basal-bolus regimen was selected, e.g. basal insulin before bedtime and prandial insulin before meals. Patients were instructed in insulin injection technique at the beginning of each treatment arm. Endpoints are assessed during the last 9 months of each treatment arm, the first 3 months being used for run-in on a new treatment regimen. Optional admissions for overnight plasma glucose measurements followed by three days of blinded continuous glucose monitoring (CGM) are performed after 6 and 12 months of treatment in each treatment arm.

**Figure 1 F1:**
[figure not shown]
Graphic presentation of the HypoAna study which is a prospective randomised cross-over study of the effect of insulin analogues and human insulin on the frequency of severe hypoglycaemia in patients with type 1 diabetes and recurrent hypoglycaemia.

### Subjects

From November 2006 to June 2007 questionnaires were sent to 6112 patients with type 1 diabetes attending the outpatient clinics at Steno Diabetes Center, Hillerød Hospital, Hvidovre Hospital, Bispebjerg Hospital, Odense University Hospital, Copenhagen University Hospital (Rigshospitalet), and Aarhus University Hospital. From some centres reminders were sent once. A total of 3861 patients filled in the questionnaire (63.2%). Patients were, among other things, asked how many episodes of severe hypoglycaemia they had experienced during the last year. Patients with two or more episodes were identified (n = 720) and invited by letter to participate in the HypoAna Trial. Subjects were included in the HypoAna Trial from May 2007 to November 2009. The inclusion criteria are type 1 diabetes for more than five years, two or more episodes of severe hypoglycaemia in the previous year (defined as need for third party assistance to restore blood glucose level), age > 18 years, and a negative pregnancy test. There were no inclusion criteria regarding the pre-randomisation insulin treatment. Exclusion criteria are treated adrenal or growth hormone insufficiency or untreated hypothyroidism, myocardial infarction or coronary revascularisation, transient ischemic attack or stroke within the last three months, history of malignancy unless a disease-free period exceeding five years, history of alcohol or drug abuse, pregnancy or lactation, and women of childbearing potential who are not using chemical or mechanical contraception. Criteria for discontinuation are voluntary withdrawal of consent, pregnancy, or non-compliance with the study protocol as judged by the investigator. Discontinuing patients are not substituted, but data on discontinuing patients are included in data analyses on an intention-to-treat basis. The study was approved by The Regional Committee on Biomedical Research Ethics (# H-KA-20070008) and the Danish Medicines Agency (# 2612–3397). The study is registered at http://www.clinicaltrials.gov (# NCT00346996). The Study will be conducted in accordance with the Helsinki Declaration.

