
### Endpoint registration

#### Severe hypoglycaemia

In case of a suspected episode of severe hypoglycaemia, patients are instructed to make a telephone call within 24 hours to a call center served by a trained diabetes nurse. The nurse performs a structured interview with the patient to validate the severity (need for assistance from others) and the plausibility of the event according to Whipple’s triad: I) characteristic hypoglycaemic symptoms; II) biochemical confirmation with plasma glucose ≤ 3.9 mmol/l; and III) adequate response to treatment with carbohydrates, glucose or glucagon. According to Whipple’s triad only episodes fulfilling all criteria can be considered definite, whereas those fulfilling two criteria can only be considered probable. Questions about time, place, blood glucose, possible cause(s) of hypoglycaemia, and types of help given to the patient are asked along with questions about health-related quality of life and questions about any consequences of the episode regarding physical or material damage and work-related absenteeism. Furthermore, at every visit to the outpatient clinic patients are asked if they have experienced any episodes of severe hypoglycaemia not recorded by telephone interview. In such cases an interview is carried out by the patient’s doctor or nurse using the same questionnaire as mentioned above. All telephone interviews are done by the same two study nurses (blinded to the treatment modality) located at Hillerød Hospital. Data from the last 9 months of each treatment arm will be used for endpoint analyses.

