### Statistics

The crossover design makes it possible to compare the two treatment modalities within the same person, thereby minimising between-patient variation. This design is appropriate because type 1 diabetes is a chronic, stable disease with slow progression. Therefore, the status of the patient in the first treatment period is assumed to be the same in the second period. To avoid a possible period effect and unwelcome fluctuations in blood glucose in relation to shift from one treatment modality to the next, registration of the primary endpoint is performed after three months in each arm. The long participation of two years per patient ensures a sufficient time of observation to minimise the risk of dealing with patients at particularly good or bad periods of their illness. Therefore, the analysis will be based on data from patients who complete the first treatment period and at least 6 months of the second treatment period. An analysis in a negative binomial distribution or Poisson model will be used to describe the number of events through a log link function as a linear function of treatment, treatment period, HbA_1c_ levels and other relevant variables (state of hypoglycaemia awareness, C-peptide status, age, duration of diabetes, daily insulin dose). Individual differences in the observation period will be adjusted for in the analysis.

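### Open-label discontinuation for investigator-judged non-compliance may end observation of severe hypoglycaemia: the plan does not separate it from leaving follow-up, and its two rules on analysing discontinued patients conflict

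*Protocol article*

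**What the plan says.** All places are in the protocol article.

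- **Design.** The trial is a "randomised, open, blinded endpoint (PROBE), multicentre, cross-over trial". Investigator and patient know the insulin.
- **Subjects.** Three criteria for discontinuation stand in one list: withdrawn consent, pregnancy, and "non-compliance with the study protocol as judged by the investigator". The next sentence reads: "Discontinuing patients are not substituted, but data on discontinuing patients are included in data analyses on an intention-to-treat basis".
- **Severe hypoglycaemia.** Events arrive by two routes. In the first, "patients are instructed to make a telephone call within 24 hours to a call center served by a trained diabetes nurse". In the second, "at every visit to the outpatient clinic patients are asked if they have experienced any episodes of severe hypoglycaemia not recorded by telephone interview". Visits are three-monthly (Experimental protocol). No source that works without the patient is named. The two telephone nurses are blinded to treatment.
- **Statistics.** The analysis is based on "patients who complete the first treatment period and at least 6 months of the second treatment period", with adjustment for differences in observation time.
- **Power calculation.** 315 patients are needed; 370 are to be included, allowing for 15% dropout.
- **Timeline.** The last visit of the last patient was in November 2011.

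**The concern.** Stopping the allocated insulin and ceasing to be observed are different events, and the plan has one word for both. Withdrawn consent does end observation. A judgement that the patient is not complying need not, yet it sits in the same list.

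The judgement is made by someone who knows the insulin and, because doses are adjusted at the investigator's discretion, follows each patient's course closely. A patient who does badly on one insulin has a reason to lapse. Removal can therefore depend on both the outcome and the insulin. Both capture routes need the patient to keep taking part, so if removal ends participation, later episodes go unseen. So do episodes since the last visit that were not telephoned in, unless someone asks at a last contact.

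The blinded nurses protect the classification of episodes that are reported. They have no part in deciding who is discontinued.

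**Working it through.** **1. The plan's own figures.** An exact two-sided 5% binomial test of p = 0.5 against p = 1/(1 + 0.85) = 0.5405 has 80.5% power at 1220 events, so the stated 80% reproduces. Patients: 1220/(2.09 + 2.09 × 0.85) = 315.5, stated as 315. Dropout: 315/0.85 = 370.6, stated as 370. None of these figures is in dispute. The allowance is 370 − 315 = 55 patients, or about 55 × 3.84 = 211 expected endpoint events. It protects precision; it does not remove bias.

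**2. Subjects against Statistics.** Completing period 1 takes 12 months, and 6 months of period 2 brings the patient to month 18.

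| Discontinued | Under Subjects | Under Statistics |
|---|---|---|
| Before month 18 | Recorded events included; later events only if collected | Whole patient left out, recorded events too |
| Months 18 to 24 | Same | Kept, with shorter observation time |

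The two statements cannot both govern the same analysis.

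**3. One patient.** Take removal at month 6 of period 1, at 2.8 events per year on both insulins.

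- Endpoint time lost on the current insulin: 12 − 6 = 6 months, or 6/12 × 2.8 = 1.4 events.
- Endpoint time lost on the other insulin: 9 months, or 9/12 × 2.8 = 2.1 events.
- Together: 15 months, or 3.5 events.

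More time is lost on the other insulin than on the current one, so this example shows lost information and not a bias against one insulin.

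**4. Illustration of bias.** These assumptions are not in the documents.

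- Mean 2.09 events per 9-month window on human insulin.
- Patient rates vary by a gamma frailty with variance 1 or 2.
- A patient with two or more events in the first half of a window is removed with probability 5% on one insulin and 15% or 20% on the other. About 1% of all patients are then removed on the first and about 3 to 5% on the second.
- 400,000 simulated patients per scenario. With nobody removed, the simulated ratio is within about 0.003 of the true one.

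| True ratio (analogue/human) | Equal removal (10% and 10%) | Unequal, completers only | Unequal, observed time |
|---|---|---|---|
| 1.00 | 1.000 to 1.001 | 0.980 to 1.020 | 0.971 to 1.031 |
| 0.85 | 0.848 to 0.852 | 0.831 to 0.868 | 0.825 to 0.874 |

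The insulin with more removals looks better. Dividing by observed time does not correct this, because patients with high counts supply less time on that insulin. The model is simplified in two ways. Observed-time results keep the other period whole. The completer set also drops patients removed midway through the period 2 window (month 3 + 4.5 = 7.5), whom the Statistics rule would keep.

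The largest shift from 1.00 is about 0.03, a fifth of the 15% minimal relevant difference (0.03/0.15).

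**The case against.** The strongest reply is that the article never says capture stops at discontinuation. Its intention-to-treat sentence is compatible with continued follow-up, and a full protocol may define non-compliance and provide a last contact. This stands in part. That later events are lost is an inference, resting on the shared list with withdrawn consent, the remark that patients are not substituted, and the dropout allowance. It does not remove the point: the criterion itself is stated, and so is the conflict with Statistics.

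A reader might also infer that removals will differ by insulin. Nothing in the document shows this. No passage says that missed glucose profiles or 3 a.m. tests count as non-compliance, and no threshold for it is given.

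A reader might further reach for a larger bias. Suppose a share f of patients has twice the rate on insulin X, and all of them are removed from X. The true ratio (1 − f) × 1 + f × 2 = 1 + f would then be seen as 1.00, a shift of 3 to 10% for f of 3 to 10%. This requires every affected patient's data on X to vanish completely. At f = 10%, two thirds of the 15% dropout would have to be outcome-related removals on a single insulin. The document supports neither assumption.

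Finally, the time adjustment and the blinded nurses may be offered as safeguards. Neither prevents the problem, for the reasons given above.

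**Conclusion.** The point holds in a limited form. In an open trial, an unmasked judgement can lead to discontinuation, both routes for the primary event need the patient's participation, and the plan does not say that observation continues. Outcome-related loss is therefore possible. Subjects and Statistics contradict each other on whether discontinued patients are analysed, and the Statistics rule makes any loss worse by discarding events already recorded before month 18.

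The size and direction of any bias are unknown. Modest differential removal moves a true ratio of 1.00 to about 0.97 to 1.03, and 0.85 to about 0.83 to 0.87, on assumptions that the document neither gives nor excludes. Equal removal on the two insulins gives no visible bias. This calls for a cheap improvement and does not show that the trial's result would be wrong.

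**What to change.** - State that discontinuation for judged non-compliance does not end endpoint follow-up.
- Unless consent is withdrawn, continue call-centre reporting and the three-monthly severe-episode question to month 24, and record the insulin in use.
- At last contact with anyone leaving, ask about severe episodes not yet reported.
- Reconcile Subjects with Statistics, and include these data in the intention-to-treat analysis. An analysis limited to patients who reach month 18 can be shown beside it.
- Report discontinuations by insulin, period and reason.

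The cost is small where follow-up is still running, since the call centre, interview form and visits exist. Some follow-up will be off the allocated insulin, which may dilute the estimated difference. The Timeline section shows that visits have ended, so prospective capture can no longer be added. Including all data already collected and reporting by insulin, period and reason remain possible. No change is proposed to when insulin treatment is stopped.
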